#### Mediation

Mediators of the treatment effects for IR and IE will be analyzed according to the following steps: (1) mediator variables, which show a change during the course of treatment, will be included in the statistical model. For this purpose, the means across and within subjects over time will be inspected for all eight proposed mediators. In order to reduce the number of relevant mediator variables, we will inspect the association between the proposed mediators over time. A composite score will be calculated for those mediator variables that are highly associated with each other if their theoretical conceptualization allows for it. (2) In a series of separate mixed regression analyses, statistically relevant mediator variables will be selected from the remaining mediator variables. To that end, the effect of each mediator on treatment outcome will be explored regardless of treatment condition. Each mediator score (measured the day after pre-assessment and after all treatment sessions) will be used to predict treatment outcome at the following assessment (i.e., 6 days/nights later). (3) Only those mediator variables that have an effect on treatment outcome will subsequently be added to a final mixed regression model, taking treatment condition into account. Fixed factors in the model will, therefore, include: treatment condition (IE and IR), relevant mediators, time, and their interaction, as well as any relevant covariate that might reduce error. The covariance structure of the repeated part will be determined by empirically assessing the best fitting structure. If possible, random parts on the participant level will be added. Note that if a mediator represents a working mechanism, the strength of the association between mediator and effect (i.e., outcome) should be similar in all conditions [71]. Therefore, to investigate whether there is a difference between the working mechanisms of IR and IE, we will test whether the mean change for each mediator differs between treatment conditions (i.e., the larger the change, the more the treatment affects the mediator, indicating that the working mechanism is strongly triggered by the treatment). Also, we will inspect the percentage of variance of the clinical effect explained by each mediator, and whether treatments differ in the percentage of variance explained by a specific mediator. (4) In a last step, all previously determined relevant mediator variables will subsequently be tested with separate mediation analyses for IE and IR (with WL as a reference group). Difference scores of mediator assessments will be used to predict post-assessment outcomes. Pre-treatment levels of the dependent and mediator variables will be added to the model as covariates (see also [64]). Both single and multiple mediation analyses will be performed. Mediation will be tested by evaluating the 95 % confidence interval of the indirect effect (i.e., the effect of the intervention (IE or IR) on treatment outcome through a specific mediator). For these analyses, we will use bootstrapping [72, 73], a nonparametrical procedure that produces an estimate of the sample distribution based on several resamples. For the proposed analyses, a minimum of *n* = 5000 bootstrap resamples will be generated. To the best of our knowledge, bootstrap mediation is currently not available for mixed regression. Unless such a technique is available by the time of the analyses, we will execute the bootstrap mediation test on the subsample with complete data, as well as on the complete sample with missing values imputed, to check for consistency of results. A multiple imputation procedure based on 20 datasets will be used to replace missing values.

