### Sample size

The proposed study was powered to detect differences between the treatments (i.e., IR and IE) compared to the WL condition. A power calculation (two-sided, power = 80 %, alpha = 0.05; G*Power 3.1) with a medium to large effect size for individual nightmare therapy (*d* = .74; [10]) showed that 30 participants in each condition would suffice to detect a statistically significant difference between each of the two treatment conditions and the WL condition. Thus, a total of 90 participants will be included in the proposed study and potential dropouts will be replaced.

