The study has several methodological strengths. First, it follows the standard for evaluating the efficacy of psychological treatments (e.g., randomization of participants to three conditions, including a waiting-list control condition, allocation is concealed by means of randomization by independent staff members, post-assessment conducted by blinded researchers). Second, the current research design is well-suited to study mediators of change for the treatment effect of IR and/or IE for nightmare disorder, which might be a first step toward identifying possible mechanisms of change for these treatments [20]. More specifically, measuring several potential mediators simultaneously at multiple time points throughout the trial (i.e., preceding the intermediate treatment effect assessments) allows us to establish temporal as well as causal relationships between proposed mediators and therapeutic outcome measures [20, 21]. Another advantage of the proposed study is its use of stripped-down treatment formats. This method enables us to gather relevant information about the efficacy of specific treatment techniques (i.e., IR and IE) rather than nonspecific treatment components (e.g., nightmare journals, relaxation exercises, extensive psychoeducation about sleep and nightmares). Accordingly, the proposed trial does not aspire to design the most efficacious treatment package for nightmare disorder, but it rather aims to investigate the efficacy of the separate treatment components, and to explore differences and similarities in efficacy and working mechanisms between rescripting-based and exposure-based nightmare treatments. In order to draw conclusions about the active component of nightmare therapies, we find it important to study the two treatment techniques in isolation. Once we have examined the two techniques separately, future studies should concentrate on creating the optimal treatment package for nightmare disorder.

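### The step 2 mediator screen leaves out the outcome recorded the day before the mediator, so it cannot separate mediator-led from outcome-led change

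*Protocol article*

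**What the plan says.** **Timing.** The primary outcomes (number of nightmares on the NFQ, and the NDIQ sum score) are completed at the start of each session and appear at every visit T1 to T5 in Table 1. The online mediator questionnaire follows one day later (Abstract; Procedure; Mediators of change). It covers seven of the eight mediators. The eighth, reduction in SUDs, comes from the imagery exercise at the start of the session (Imagery exercise).

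**Analysis** (Statistical methods, Mediation):

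- Step 2: "Each mediator score (measured the day after pre-assessment and after all treatment sessions) will be used to predict treatment outcome at the following assessment", about six days later. Arms are pooled: "the effect of each mediator on treatment outcome will be explored regardless of treatment condition". No covariate is named.
- Step 3: "Only those mediator variables that have an effect on treatment outcome will subsequently be added to a final mixed regression model". Its fixed factors are condition, the retained mediators, time and interaction, plus unspecified covariates that lower residual error.
- Step 4: mediator difference scores predict the post-assessment outcome, for IE and IR separately against the waiting list, adjusted for the pre-treatment outcome and mediator.

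**Interpretation.** The Discussion says that measuring mediators ahead of the intermediate outcomes "allows us to establish temporal as well as causal relationships between proposed mediators and therapeutic outcome measures".

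**The concern.** Measuring the mediator before the next outcome gives useful time order only if the outcome already reached at that point is held constant. Otherwise two accounts give the same step 2 result: the mediator changes and nightmares then fall, or nightmares have already fallen and the mediator reflects it. Because severity persists, the second account also makes the mediator predict the following week.

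Some items invite this. The nightmare distress mediator asks about negative influence on daily functioning (Table 2), and the NDIQ daytime subscale has an item on not functioning properly during the day.

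Mechanism is a stated objective with its own planned paper. At stake is whether the mediators reported as relevant are more than markers of current severity.

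**Working it through.** **The plan's own figure.** The document states that "30 participants in each condition would suffice to detect a statistically significant difference". Normal approximation: n = 2(1.96 + 0.8416)² / 0.74² = 15.70 / 0.5476 = 28.7, so 29 per arm. The two-sample t-test gives 29.66, so 30 per arm, with power 80.5%. The stated 30 reproduces. The present point does not touch it and only takes N = 90 from it.

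**Inputs from the document.** N = 90 (60 treated, 30 waiting list), five weekly outcomes and therefore four lagged pairs per person (T1→T2 to T4→T5), and a treatment effect of 0.74 SD by T5.

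**Assumed, because the document gives no values.** Correlation ρ of mediator with current outcome 0.3–0.7; within-person autocorrelation φ 0.3–0.5; between-person variance share ICC 0–0.5; random-slope SD 0–0.2; outcome approximately normal; passing means p < 0.05, since step 2 states no threshold.

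**Model of a pure follower.** Y(t) = person intercept + slope × t + AR(1) error, and M(t) = ρY(t) + √(1 − ρ²) × noise. Nothing runs from M to any later Y.

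**Algebra (slopes set aside, unit variances).** The lag-one correlation of Y is r = ICC + (1 − ICC)φ. Regressing Y(t+1) on M(t) alone gives a coefficient of ρ × r. With ρ = 0.5, ICC = 0.5 and φ = 0.3, r = 0.5 + 0.5 × 0.3 = 0.65 and the coefficient is 0.325. With ρ = 0.3 it is 0.195. Once Y(t) is in the model, what is left of M(t) is pure noise and the coefficient is 0.

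**Simulation, 300 runs per row.** Share of runs in which the follower passes (RI = random-intercept mixed model; CR = no random intercept, cluster-robust standard errors):

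| ρ | φ | ICC | slope SD | RI, without Y(t) | RI, with Y(t) | CR, without Y(t) | CR, with Y(t) |
|---|---|---|---|---|---|---|---|
| 0.3 | 0.3 | 0.5 | 0.1 | 20% | 3% | 96% | 6% |
| 0.5 | 0.3 | 0.5 | 0.1 | 40% | 3% | 100% | 6% |
| 0.5 | 0.5 | 0.3 | 0.2 | 80% | 2% | 100% | 3% |
| 0.5 | 0.5 | 0.5 | 0 | 61% | 3% | 100% | 5% |
| 0.7 | 0.5 | 0.5 | 0.2 | 98% | 4% | 100% | 5% |
| 0.5 | 0.5 | 0 | 0 | 16% | 1% | 100% | 4% |
| 0.5 | 0.5 | 0 | 0, outcome error SD 0.5 | 15% | 6% | 100% | 16% |

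Monte Carlo standard error: √(0.05 × 0.95 / 300) = 1.3 points near 5%, and √(0.25 / 300) = 2.9 points near 50%. A separate check over other assumed values gave 85–100% without a random intercept. One scenario with 60 treated participants only (ρ = 0.3, φ = 0.3, ICC = 0.5, slope SD 0.1) gave 10% (RI) and 84% (CR), falling to 3% and 4% with Y(t).

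**What adjustment cannot do.** The last row shows that error in the measured outcome leaves up to 16%. In a scenario where an unmeasured severity drives both variables, about 66% still passed after adjustment.

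**Does step 4 repair it?** Step 4 was simulated as IE against waiting list, 30 per arm, with baseline covariates, a follower at ρ = 0.5–0.7 and 400 trials per scenario. The bootstrap interval for the indirect effect excluded zero in 7–33% of trials when the mediator change ended one day after the third session, and in about 1% or less once the T4 outcome was added. Baseline adjustment alone is therefore not a reliable repair.

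**The case against.** The fair case for the plan is this. The prior outcome is unnamed, not excluded, and step 3 leaves room for further covariates. Mediation is described as exploratory in several places, and step 2 calls its survivors statistically relevant, not causal. Step 2 is a mixed regression, and a random intercept, planned where possible (stated for step 3), lowers the pass rate considerably. The primary efficacy comparison is untouched.

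All of that stands, but it does not answer the point. The article lists factors for step 3 and covariates for step 4, and the preceding outcome is in neither list. A provision for reducing error does not commit to controlling this confounder. With a random intercept the rate was still 15% or more at N = 90.

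Four stronger readings are tempting, and the documents do not support them:

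- *Every follower is certain to pass.* Rates near 100% belong mainly to models without a random intercept. Those were fitted with cluster-robust errors, which is not the planned mixed model.
- *Leaving condition out of step 2 is a separate fatal flaw.* Condition enters in step 3 and the waiting-list contrast in step 4. In a simulation with autocorrelation and mediator correlation both 0.6, adding condition by time did not change the pass rate.
- *Screening on the same data invalidates the step 4 intervals.* In a check with no mediator effect, requiring both paths to be significant (a proxy for the planned indirect-effect interval) gave 4% and 3% among screened-in mediators. Inflation of the planned test is not shown.
- *The article promises causal pathways throughout.* Only one Discussion clause plainly claims causality. The closing paragraph treats temporal relationships as a requirement for causal pathways, which is a weaker statement.

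**Conclusion.** The point holds. As specified, step 2 cannot separate change led by the mediator from change led by the outcome. A mediator with no effect on later outcome passes well above 5%: about 15–98% with a random intercept and 85–100% without. These ranges rest on assumed correlations, a normal outcome and a 5% threshold. Nightmare counts under Poisson or negative binomial models would give different figures, but the mechanism is the same. Adding the preceding outcome restores roughly nominal rates when the mediator follows the measured outcome. It does not do so when unmeasured severity or outcome error is at work.

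The one-day ordering applies to the seven online scales and not to SUDs. Weekly prior values exist for NFQ and NDIQ, but not for ZIL, ISI or NBQ, which are taken only at T1, T5 and the follow-ups. The consequence is confined to the mechanism objective.

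**What to change.** 1. In steps 2 and 3, for the weekly primary outcomes (NFQ number of nightmares and NDIQ), add as a covariate the outcome from the appointment one day before the mediator, with condition and time in the model.
2. For reduction in SUDs, treat the same-session outcome as concurrent and make no claim that one precedes the other.
3. In the Discussion, replace the claim of temporal and causal relationships with one of temporal associations.

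Testing the four hypothesised mediators (distress and tolerability for IE, valence and mastery for IR) whatever the screen shows is optional.

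Cost: wording only, since Table 1 already has both primary outcomes at every visit T1 to T5. The price is weaker apparent mediator effects. The outcome is completed at the start of the session, so adjusting for it does not remove the mediator's response to that same session.

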
Taken together, the proposed project offers a unique opportunity to investigate the efficacy of two core treatment techniques for nightmares (IR and IE), and to explore and identify their mechanisms of change. More specifically, by including mediator and outcome variable assessments at multiple time points throughout the study, we intent to investigate temporal relationships between changes in mediators and their effects on outcome measures, which are needed to determine causal pathways of therapeutic change. Thus, with the proposed trial, we aim to provide new insights in the mechanisms of change of IR and IE for nightmares and thereby contribute to the improvement of such treatments. Moreover, given that rescripting as well as exposure techniques are also used in the treatment of other disorders, the results of the current study might provide useful knowledge about the working mechanism of these therapeutic techniques in general.

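### Mediation steps 2 and 3 use the raw weekly mediator score without pre-treatment adjustment, so the screen and the step 3 association can pick up stable severity differences instead of change

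*Protocol article*

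**What the plan says.** All of this stands in the protocol article, Statistical methods, Mediation, unless noted.

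- **Step 1** keeps mediators that change during treatment: "the means across and within subjects over time will be inspected for all eight proposed mediators". This is inspection; no within-person model is fitted.
- **Step 2** lags the weekly score onto the next outcome: "Each mediator score (measured the day after pre-assessment and after all treatment sessions) will be used to predict treatment outcome at the following assessment". The association is pooled: "the effect of each mediator on treatment outcome will be explored regardless of treatment condition".
- **Step 2 is a gate**: "Only those mediator variables that have an effect on treatment outcome will subsequently be added to a final mixed regression model".
- **Step 3** lists as fixed factors "treatment condition (IE and IR), relevant mediators, time, and their interaction, as well as any relevant covariate that might reduce error". Random effects are conditional: "If possible, random parts on the participant level will be added". The step also compares mean mediator change between IE and IR, and inspects the percentage of variance that each mediator explains.
- **Step 4**, the bootstrap test of the indirect effect against waiting list, changes the predictor: "Difference scores of mediator assessments will be used to predict post-assessment outcomes". It adds the pre-treatment mediator and outcome as covariates. That adjustment is stated for step 4 only.
- **The Discussion** says the repeated assessments serve to "investigate temporal relationships between changes in mediators and their effects on outcome measures" and treats this as the route to causal pathways.

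**The concern.** The question put to the weekly data is whether a change in a mediator precedes a change in outcome. Its null hypothesis is no within-person relation. A raw repeated score entered as one predictor tests something wider: no association within people and none between people.

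Stable between-person association is plausible here. The nightmare-distress mediator item (Table 2) asks about daily functioning, as does the example item of the daytime subscale of the NDIQ, a primary outcome. The sleep-quality mediator is close to the example item of the NDIQ night subscale. Someone with severe nightmares may score badly on both every week, whatever treatment does.

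Steps 2 and 3 are the only steps that state lagged weekly pairs, the feature that the Discussion presents as a strength. At stake are which mediators pass the gate, and whether a step 3 coefficient or percentage of variance is read as an effect of change.

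**Working it through.** **Inputs from the protocol article.** Mediators are taken one day after T1 to T4 and predict outcomes at T2 to T5 (Table 1 note; step 2), giving J = 4 lagged pairs per person. There are 30 participants per condition. Step 2 can use up to 90; step 3 names only IE and IR, so about 60. The article gives no error rate for the mediator screen to reproduce. Its sample-size figure does reproduce (d = 0.74, two-sided 0.05, 80% power: n = 29.66, so 30 per arm), but it concerns the treatment comparison and supplies only N here.

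**Assumptions (not in the article).** Normal outcome, unit variances, equal ICC for mediator and outcome, correlation rho between their stable person levels, true within-person effect zero, and at first no feedback from outcome to mediator.

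**Hand check at ICC = 0.5, rho = 0.5, random intercept included.**

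1. Between-person slope = rho × ICC / (ICC + (1 − ICC)/J) = 0.25 / 0.625 = 0.40.
2. Information per person: within = J − 1 = 3; between = J × 0.625 / (0.5 + 4 × 0.5) = 2.5/2.5 = 1. Weight on the between-person slope = 1/(3 + 1) = 0.25.
3. Expected raw slope = 0.25 × 0.40 + 0.75 × 0 = 0.10 SD per SD, although the true effect of change is zero.
4. Standard error = 1/√(4N): 0.0645 at N = 60 and 0.0527 at N = 90. So z = 1.55 and 1.90, and rejection is about 0.34 and 0.48.
5. At rho = 0.3: between-person slope 0.15/0.625 = 0.24, raw slope 0.06, z = 0.93 and 1.14, rejection about 0.15 and 0.21.

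Simulation of the same cells (400 runs each, time dummies, random intercept) gave slopes of 0.104 and 0.105 at rho 0.5, with rejection 0.38 and 0.515. At rho 0.3 rejection was 0.145 and 0.212. The hand figures run slightly low at rho 0.5 because the mediator itself absorbs between-person outcome variance, which raises the weight in step 2.

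**Simulated rejection at nominal 5%, raw score, ICC 0.3 to 0.7:**

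| rho | N = 60 | N = 90 |
|---|---|---|
| 0 | 3–5% | 5–6% |
| 0.3 | 10–19% | 15–26% |
| 0.5 | 25–47% | 34–62% |
| 0.7 | 48–80% | 60–94% |

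A separate simulation over ICC 0.4 to 0.6 and N = 60 to 90 gave 16–22% at rho 0.3 and 36–63% at rho 0.5. With 400 runs the Monte Carlo standard error is √(0.16 × 0.84/400) = 1.8 points to √(0.5 × 0.5/400) = 2.5 points.

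**Alternatives under the same null.**

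- Raw score plus pre-treatment outcome (N = 60, rho 0.5): 20–26%. A partial cure.
- Step-4-type regression (T5 outcome on mediator difference, pre-treatment mediator and outcome; N = 60): 6–7% at rho 0.3, 8–9% at 0.5, 13–17% at 0.7.
- Person mean plus weekly deviation, tested on the deviation: 4–5% without feedback. With an assumed 0.3 of each week's outcome deviation carried into the next-day mediator, it rejects at 15–25% with negative slopes.
- Pre-treatment mediator plus change from it, with pre-treatment outcome, tested on the change term: 3–13% with and without that feedback.

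Feedback also pulls the raw slope down. With an assumed carry-over of 0.3 to 0.5 and rho 0.3 to 0.5, one set of runs put the raw model at 6–20%; another set with feedback gave 15–28%.

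**The case against.** **Steps 2 and 3 do not decide mediation.** Step 1 drops mediators that do not move, and step 4 is the formal test, with difference scores, pre-treatment covariates and a bootstrap interval. A reader might infer that the plan will declare severity markers to be mediators. The article does not support that: a false pass in step 2 sends one more candidate to a test of change. The step 3 comparison of mean mediator change is also untouched. This stands and limits the reach of the point. It does not remove it. A mediator can change on average and still carry stable differences between people, and the step 3 association and percentage of variance explained are read in their own right.

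**The article leaves room.** Covariates that reduce error are allowed, nothing forbids centring, and the aim is exploratory with conceded low power for differences in mediators. However, the same paragraph states difference scores and pre-treatment covariates for step 4 and raw scores for step 2. The allowance is for reducing error, and the most obvious such covariate, the pre-treatment outcome, helps only in part.

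**Person-mean centring would be the obvious cure.** A reader might infer that it is clean. It is not safe here, because each mediator is taken one day after an outcome assessment and the items overlap in content. Feedback from outcome to mediator is therefore plausible, and with four occasions it biases the weekly deviation. This stands and shapes the fix.

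**Conclusion.** The point holds for the step 2 screen and for the step 3 association and percentage of variance explained. With a true within-person effect of zero, ICC 0.4 to 0.6 and no outcome-to-mediator feedback, false selection is about 16–22% at a between-person correlation of 0.3 and 36–63% at 0.5, for 60 to 90 participants. Without that correlation, and without feedback, there is no inflation; with feedback the two biases partly offset. The ICC, correlation and feedback are assumptions, so the direction is firmer than the size. The check used a normal outcome; nightmare frequency will have a count model, where the mixing argument carries over but these percentages need not.

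Step 4 is largely, though not wholly, protected, and the comparison of mean mediator change is unaffected. The mediation aim as a whole is not invalidated. The change is worth making because the Discussion reads the lagged data as effects of change.

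**What to change.** In steps 2 and 3:

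- Enter each mediator as two terms: its pre-treatment level (the score one day after pre-assessment) and the change from that level.
- Add the pre-treatment outcome as a covariate, as step 4 already does.
- Select mediators, and interpret the temporal association, on the change term only.
- Report the split into person mean and weekly deviation as a sensitivity analysis only, stating that with four occasions it is biased if the outcome feeds back into the next-day mediator score.

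**Cost.** No new data: one derived variable per mediator and a few lines of text. The interval for the change term will be somewhat wider, partly because change is zero for everyone at the first lagged pair. A small residual between-person bias remains (rejection about 3–13% in the simulations above), so a selected mediator still needs step 4 behind it.

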Against this background, we designed and developed treatment protocols, which consist mainly of either rescripting of, or exposure to, the nightmare content. Such stripped-down versions of exposure and rescripting for nightmares allow us to investigate the therapeutic efficacy of these treatments without any (possibly distorting) influence of nonspecific treatment components. While knowledge about the efficacy of pure rescripting and exposure for nightmares might be valuable to appraise the importance of different processes underlying psychological treatments for chronic nightmares, stripped-down treatment protocols have another significant advantage. Namely, using stripped-down versions of IE and IR in the treatment of nightmares may help to identify their mediating mechanisms. Thus, in order to (1) identify mediators of the treatment effect that (uniquely) contribute to the efficacy of IE versus IR, we aim to (2) establish the efficacy of each of these stripped-down treatments when compared to a waiting-list control group. In line with previous research, it is hypothesized that both treatments will effectively reduce nightmare symptoms [10, 11]. Potential differences between IR and IE will be explored. With regard to the mechanisms of change, we assume that both treatments target different key processes. This assumption is mainly based on current theories about the working mechanisms of IR and IE for nightmares. Specifically, we hypothesize that nightmare distress and tolerability of emotions elicited by nightmares might be critical mediating variables of the treatment effect of IE. In contrast, nightmare valence and mastery of the nightmare content might be particularly important mediators of the treatment effect in IR. However, given the limited empirical knowledge about the underlying mechanisms of nightmare treatments (especially IR), we cannot exclude the possibility that a number of the selected mediators might play a critical role in both treatments (e.g., predictability and controllability of emotions elicited by nightmares, and sleep quality), rather than being exclusive to either IR or IE. Therefore, we will further explore if the proposed variables play a unique role in either rescripting-based or exposure-based nightmare treatments, or whether they could be relevant mediators of therapeutic change in both therapies.

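### The four hypothesised mediator–treatment pairs are not kept apart from the exploratory set: all eight mediators share one data-driven selection and an unadjusted 95% test, so the hypotheses have no guaranteed test

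*Protocol article*

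**What the plan says.** Trial objectives makes identification of mediators aim (1) and separates two classes. The first is hypothesised: "we hypothesize that nightmare distress and tolerability of emotions elicited by nightmares might be critical mediating variables of the treatment effect of IE", while "nightmare valence and mastery of the nightmare content might be particularly important mediators of the treatment effect in IR". The second, whether the proposed variables matter in one treatment or in both, is left to exploration.

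The Mediation section describes a single route for all eight mediators:

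- **Step 1:** mean change is inspected, and mediators that are strongly associated may be combined into a composite where theory permits. No cut-off is given.
- **Step 2:** each remaining mediator is used to predict the next outcome assessment, ignoring treatment condition.
- **Step 3:** "Only those mediator variables that have an effect on treatment outcome will subsequently be added to a final mixed regression model". Mean mediator change is also compared between IR and IE.
- **Step 4:** "all previously determined relevant mediator variables will subsequently be tested with separate mediation analyses for IE and IR", against the waiting list, by a bootstrap 95% interval for the indirect effect. Single and multiple models are both run. Complete-case and imputed data are both used unless a mixed-model bootstrap becomes available.

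No step treats the four hypothesised pairs differently. The section does not say which of the two primary outcomes it means. The Discussion states that the design "allows us to establish temporal as well as causal relationships between proposed mediators and therapeutic outcome measures".

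**The concern.** Two things follow from the single route.

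First, the hypotheses can lose their test. Tolerability and controllability of emotions, for example, have almost identically worded items in Table 2 and could be merged. Tolerability in IE would then have no test of its own. A hypothesised mediator that misses the step 2 screen never reaches step 4.

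Second, the mediators that do reach step 4 are all tested at the same unadjusted level, for two treatments and possibly two outcomes. A significant indirect effect for a theory-based pair cannot be told apart from one found by searching, and the chance of at least one false finding can exceed 5%.

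At stake is aim (1), the mechanism question, and the strength of the wording in which its results may be reported. The efficacy comparisons with the waiting list are not affected.

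**Working it through.** **The plan's own figure.** Sample size gives "two-sided, power = 80 %, alpha = 0.05; G*Power 3.1", d = 0.74, and says that "30 participants in each condition would suffice to detect a statistically significant difference between each of the two treatment conditions and the WL condition". With the noncentral t distribution, the noncentrality is 0.74 × √(30/2) = 2.87 and power is 0.805 at 30 per arm (0.791 at 29). The figure of 30 reproduces. It concerns treatment against waiting list; the article states no power or error rate for mediation.

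**Number of final tests.** 8 mediators × 2 treatments = 16 indirect effects per outcome, or 32 if both primary outcomes are used. With independent tests at 5%, the chance of at least one false result is 1 − 0.95^16 = 56% and 1 − 0.95^32 = 81%. These are ceilings. They need every mediator to survive unmerged and treatment to move all of them.

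**Simulation of steps 2 and 4.** There were 2,000 trials per setting, with 3 arms of 30, eight mediators, a direct treatment effect of 0.74 SD on outcome, and no mediator affecting any outcome. Assumptions not in the article:

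- screen at p < 0.05 with a lagged random-intercept model;
- intraclass correlation 0.5;
- an indirect effect counts as significant when both paths have p < 0.05, standing in for the bootstrap.

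Step 1 and composites were not modelled.

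| Treatment shift in mediators (SD) | Mediator correlation | Outcomes | Time in screen | Non-mediators passing screen | Any false mediator, no screen | Any false mediator, with screen |
|---|---|---|---|---|---|---|
| 0 | 0 | 1 | yes | 4.9% | 4.1% | 0.2% |
| 0 | 0.5 | 1 | yes | 4.6% | 3.4% | 0.1% |
| 0 | 0.5 | 2 | no | 5.3% | 5.8% | 0.2% |
| 0.74 | 0 | 1 | yes | 8.9% | 49.4% | 5.4% |
| 0.74 | 0.5 | 1 | yes | 9.3% | 38.9% | 5.7% |
| 1.5 | 0.5 | 1 | yes | 18.6% | 41.6% | 9.6% |
| 0.74 | 0.5 | 1 | no | 22.9% | 41.2% | 12.0% |
| 1.5 | 0.5 | 1 | no | 63.4% | 41.2% | 29.0% |
| 0.74 | 0.5 | 2 | yes | 8.8% | 60.6% | 8.8% |
| 1.5 | 0.5 | 2 | yes | 19.8% | 64.6% | 18.6% |
| 0.74 | 0.5 | 2 | no | 23.7% | 60.1% | 21.3% |
| 1.5 | 0.5 | 2 | no | 62.1% | 63.5% | 46.4% |

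Time matters because the article lists it as a factor in step 3 but not in step 2. Two further simulations with a screen that ignored time gave 23–37% and 22–43% for two outcomes, and 14–23% and 15–27% for one. With no movement of the mediators and two outcomes, the rate was 1–3%.

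**What the screen does.** In every row the with-screen rate is below the no-screen rate. When treatment moves the mediators, the rate per final test among survivors stays near 4–5%. The excess therefore comes from how many final tests there are.

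**Four pairs taken straight to step 4.** On one outcome at 5% each, the independence bound is 1 − 0.95^4 = 18.5% and the simulated rate is about 14–18% when treatment moves the mediators. At 1.25% each the bound is 1 − 0.9875^4 = 4.9% and the simulated rate is 2.5–4.9%. Removing the screen for these pairs secures their test but does not by itself control error.

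**Cost of adjustment.** Interval width rises by 2.498/1.960 = 1.27, about 27%. For power, assume 30 v 30, a mediator shift of 0.74 SD, and a mediator–outcome coefficient of 0.3 to 0.5 with residual SDs of 1 (noncentrality about coefficient × √58, 57 degrees of freedom). Joint power is approximately the product of the two path powers:

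- at 5%: 0.805 × 0.613 = 0.49 to 0.805 × 0.963 = 0.77;
- at 1.25%: 0.615 × 0.392 = 0.24 to 0.615 × 0.886 = 0.54.

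Simulation under similar assumptions gave 49–76% falling to 25–52%.

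**The case against.** The strongest reply is that the mechanism aim is exploratory. The Abstract, Design and Discussion all speak of exploring mediators, the four hypotheses are worded tentatively, and multiplicity rules are commonly left to an analysis plan that is not shown. This stands against faulting the missing adjustment alone. It does not remove the structural point: the article itself prescribes the gate, and a later multiplicity rule would not bring back a pair already dropped or merged.

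A reader might infer that a false mechanism is likely. The documents do not support that. The rate comes near one half only with two outcomes, a screen that ignores time and large effects on every mediator, and it is very small if treatment moves none. Nor is the screen to blame, since it lowers the overall error. The count of 32 should not be inflated either: the complete-case run is a consistency check, and use of both primary outcomes in step 4 is an assumption.

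A reader might also infer that the hypotheses are not tested at all. That goes too far. Surviving pairs are tested separately for IE and IR, and step 3 compares mediator change between them. A pair dropped because its mediator did not change or predict outcome has lacked support on a necessary condition, though that is weak evidence at this sample size.

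Finally, a compulsory Bonferroni correction would cost much power in a small trial. That stands, and makes adjustment a choice to declare.

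**Conclusion.** The point holds in limited form. The article distinguishes four hypothesised pairs from an exploratory set, and its mediation steps then erase the distinction. The pairs have no guaranteed test and no status of their own if they survive. This rests on the text alone and needs no simulation.

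The error rate is secondary and conditional. If treatment moves the mediators and none mediates, at least one false mediator appears in roughly 5–29% of trials for one outcome and 9–46% for two. The rate depends on whether the screen accounts for time, how strongly treatment moves the mediators and how they correlate. It is at most about 3% if treatment moves none. These figures assume a 5% screen and a joint-significance stand-in for the bootstrap, and leave out step 1 and composites. Correlation between mediators and outcomes from shared self-report was not modelled and would raise them.

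The causal claim in the Discussion is too strong for a separate reason. Mediators are not randomised, so even full multiplicity control would not make the claim causal.

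**What to change.** In the Mediation section:

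1. Take the four pairs (IE: nightmare distress, tolerability; IR: valence, mastery) to step 4 as separate variables whatever steps 1 to 3 show, and keep them out of composites for that test.
2. Test them in single-mediator models on one named primary outcome, with one named lead data set, for example the imputed data.
3. Label all other mediators, outcomes and models, and the step 3 comparisons of mediator change between IR and IE, as exploratory.
4. Say which status the four have. If confirmatory, state the family-wise level (Holm, or 98.75% intervals). If not, report them as pre-specified but unadjusted.

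In the Discussion, replace the causal claim with wording limited to temporal associations consistent with mediation.

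The change is to wording only and needs no further data or participants. Findings outside the four become hypothesis-generating. If the family-wise level is adopted, 98.75% intervals are about 27% wider and power falls from roughly 49–76% to 25–52% under the assumed effects. Without it, a chance of about 14–18% of at least one false result among the four should be acknowledged for the case where treatment moves the mediators.
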